## Abstract

**Background:**

Gastrointestinal endoscopy has been associated with difficult experiences and can leave patients with an unpleasant impression. Propofol and midazolam are the most commonly used intravenous anesthetics for sedation during gastrointestinal endoscopy. However, cardiac and pulmonary adverse events are the primary concerns associated with the use of these sedatives. Remimazolam tosylate is an ultra-short-acting benzodiazepine drug with a mild inhibitory effect on the respiratory and circulatory systems. These properties qualify remimazolam tosylate to be used as a replacement for propofol or midazolam as a sedative during gastrointestinal endoscopy. This study aims to describe the efficacy and safety of remimazolam tosylate as a sedative for upper gastrointestinal endoscopy.

**Methods:**

A multicenter, randomized, single-blind, parallel-controlled, noninferiority clinical study will be conducted to evaluate the efficacy and safety of remimazolam tosylate as a sedative during upper gastrointestinal endoscopy. Participants (*n* = 1800) will be randomized to receive remimazolam tosylate at 0.15 mg/kg (experimental group 1), remimazolam tosylate at 0.2 mg/kg (experimental group 2), or propofol at 1.5 mg/kg (control group). Procedure success will be assessed and defined as the completion of upper gastrointestinal endoscopy without the administration of a rescue sedative agent or more than two top-up doses of the trial drug in any 5-min period after initial administration. Sedation quality will be evaluated using the Modified Observer’s Assessment of Alertness/Sedation score. Adverse events will be recorded to evaluate safety.

**Discussion:**

This study will determine the optimal dosage of remimazolam tosylate during upper gastrointestinal endoscopy and will describe its efficacy and safety. These findings may contribute to a more comfortable and safer experience for patients compared with that when the conventional sedative propofol is used.

**Trial registration:**

ClinicalTrials.gov NCT04727034. Registered on February 18, 2021.

**Supplementary Information:**

The online version contains supplementary material available at 10.1186/s13063-022-06935-0.

## Background

In current clinical practices, midazolam or propofol are the main anesthetic sedatives commonly used during outpatient procedures, such as gastrointestinal endoscopic diagnosis and treatment [1]. Propofol has certain advantages, including rapid onset of action, short recovery profile, antiemetic properties, equivalent amnesic effects, and patient’s comfort [2]. Therefore, propofol is frequently used as a sedative agent during standard endoscopic procedures worldwide [3]. However, it has a disadvantage in the form of a narrow therapeutic index, which potentially causes cardiovascular and respiratory depression and hypoxia, resulting in the potential need for urgent endotracheal intubation [4]. Supplemental oxygen is often necessary when propofol is used. Nonanesthesia specialists have not been authorized to use propofol in many countries, resulting in patients not benefiting from propofol.

Midazolam is a commonly used sedative during gastrointestinal endoscopy because of the lesser risk of complication and medical legal issues [5]. Midazolam metabolites, namely, 1-hydroxymidazolam and α-hydroxymidazolam, also show pharmacodynamic potential comparable to midazolam [6, 7]. There is a concern regarding the potential for repeat sedation when the active metabolite becomes bioavailable [8].

Remimazolam is a new type of narcotic and sedative that belongs to the same benzodiazepine class as midazolam [9]. Remimazolam, an ester-based drug, is designed to be rapidly hydrolyzed in the body by ubiquitous tissue esterases to an inactive carboxylic acid metabolite (CNS 7054) [10]. It is broken down to produce metabolites with significantly weakened affinity for type A gamma-aminobutyric acid (GABAA) receptors [11]. It is characterized by a more rapid offset and quicker return to normal cognitive and memory function than that of midazolam [12, 13]. Compared with propofol, remimazolam has no injection pain and has a lower incidence of hypotension [14]. In the USA, only anesthesiologists are authorized to administer propofol [15]. However, unlike propofol, remimazolam belongs to benzodiazepine, which allows it to be used without specific restrictions. Therefore, remimazolam has good application prospects in upper gastrointestinal endoscopy.

Remimazolam tosylate (RT), which acts on GABA receptors, is a new ultra-short-acting benzodiazepine [16] developed by HengRui Medicine Co., Ltd., China. Similar with remimazolam, RT has a short half-life that results in quick-acting onset and recovery compared with currently available short-acting sedatives [17]. Recent studies have reported that RT is suitable for short operations, such as gastrointestinal endoscopy, hysteroscopy, bronchoscopy, and closed reductions of long-bone fractures [18].

We will perform this randomized, single-blind, parallel-controlled, noninferiority clinical trial at five centers. Therefore, this study aims to determine the optimal dosage of remimazolam tosylate during upper gastrointestinal endoscopy and to describe its efficacy and safety in Chinese patients undergoing upper gastrointestinal endoscopy.

### Aims and objectives

Compared with propofol, the safety and efficacy of remimazolam tosylate during upper gastrointestinal endoscopy are verified based on the completion of upper gastrointestinal endoscopy, vital signs of participants, and satisfaction of endoscopists and patients.

### Trial design

A multicenter, randomized, single-blind, parallel-controlled, noninferiority study protocol was formulated. We will compare the efficacy and safety of remimazolam tosylate with those of propofol during sedation for upper gastrointestinal endoscopy. This clinical trial has been approved and is supported by the ethics committee of Renji Hospital, Shanghai Jiaotong University School of Medicine (KY2020-127).

This study was presented according to the recommendations of the Standard Protocol Items: Recommendations for Interventional Trials (SPIRIT) (Supplemental file, SPIRIT checklist). This trial was registered on 18 February 2021 in ClinicalTrials.gov, NCT04727034. The trial registration dataset is presented in the Supplemental table.

## Methods

### Participants, interventions, and outcomes

#### Study setting

This study will recruit 1800 participants from Renji Hospital, Shanghai Jiaotong University School of Medicine, Shanghai East Hospital, The First Affiliated Hospital of Nanchang University, The First Affiliated Hospital of Jiaxing University, and The Second Affiliated Hospital of Jiaxing University.

#### Eligibility criteria

Participants will be recruited primarily from the abovementioned five centers. Table 1 presents a summary of the inclusion and exclusion criteria.

**Table 1 Tab1:** Inclusion/exclusion criteria

Inclusion criteria	Exclusion criteria
(1) Age, ≤18 and ≤60 years, no gender limit	(1) Need to perform complicated endoscopic techniques for diagnosis and treatment, such as cholangiopancreatography surgery, endoscopic ultrasonography, endoscopic mucosal resection, endoscopic submucosa stripping, and oral endoscopic muscle dissection
(2) Undergoing routine upper gastrointestinal endoscopic diagnosis and treatment	(2) Intend to undergo tracheal intubation
(3) American Society of Anaeshesiologists (ASA) classification I–II	(3) Judged to have difficulty in managing the respiratory tract (modified Mallampati score is IV)
(4) 18 kg/m^2^ < body mass index (BMI) < 28 kg/m^2^	(4) Anemia or thrombocytopenia, (hemoglobin < 90 g/L, platelet count <80 × 10^9^/L)
(5) Time of upper gastrointestinal endoscopy not exceeding 30 min	(5) Diagnosed with lung diseases (asthma, bronchitis, chronic obstructive pulmonary diseases, pulmonary bullae, pulmonary embolism, pulmonary edema, and lung cancer)
(6) Clearly understand and voluntarily participate in the study; provide signed informed consent	(6) Diagnosed with liver and kidney diseases (aspartate aminotransferase and/or alanine aminotransferase ≥2.5 × upper limits of normal (ULN), total bilirubin ≥1.5 × ULN, and blood creatinine levels greater than the upper normal limit)
	(7) History of drug and/or alcohol abuse within 2 years before initiating the screening period; average daily alcohol consumption of >2 units of alcohol (1 unit = 360 mL beer or 45 mL liquor with 40% alcohol content or 150 mL grapes liquor)
	(8) Blood pressure not satisfactorily controlled by antihypertensive drugs (sitting systolic blood pressure, ≥160 mmHg during the screening period and/or diastolic pressure during the screening period pressure, ≥100 mmHg)
	(9) Sitting systolic blood pressure of ≤90 mmHg during the screening period
	(10) Pregnant or breastfeeding
	(11) Allergies or contraindication to benzodiazepines, opioids, propofol, and lidocaine
	(12) Participated in other drug clinical trials in the past 3 months
	(13) Investigator’s judgment as an unsuitable participant
	(14) Diagnosed with heart disease (heart failure, angina pectoris, myocardial infarction, and heart rhythm abnormalities)

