#### Recruitment and informed consent

Participants who are scheduled to undergo sedated upper gastrointestinal endoscopy in the outpatient gastrointestinal endoscopy operating room will be included in this study. They will be given an informed consent form, and they will be given the opportunity to review the consent and ask questions regarding the study. Interested participants will be screened using the inclusion and exclusion criteria. Eligible participants will sign an informed consent form. Study participation is voluntary, and the participants can withdraw from the study at any point of time. The recruitment and consent of the study participants by the members of the research team are in accordance with the Good Clinical Practice (GCP) guidelines. During the clinical trial, researchers will immediately report any serious adverse events occurring in the participants to the director-in-charge of the clinical trial of the research institution and will contact [name] or [name].

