##### Additional analyses

Subgroup analysis: Subgroup analysis via an interaction by gender, age (18–24, 25–44, and 45–60 years), and BMI (<23 and ≥23 kg/m^2^) will be used to analyze the primary and secondary outcomes among subgroups.Safety analysis: General safety evaluations will be based on the incidence and type of adverse events. Safety variables will be tabulated and presented for all participants in the safety set. Adverse events will be coded using the World SIVA adverse sedation event reporting tool. The number (%) of participants with any adverse events will be summarized.

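### The age criterion in Table 1 carries a wrong inequality sign: as printed it admits only people aged 18 or younger and contradicts the planned 18–60 age subgroups

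*Protocol article*

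**What the plan says.** Table 1, under Eligibility criteria in the protocol article, gives the first inclusion criterion as "1) Age, ≤18 and ≤60 years, no gender limit". The section on recruitment and informed consent puts the table to use: "Interested participants will be screened using the inclusion and exclusion criteria".

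The only other indication of the intended age range is the subgroup plan under Additional analyses, which splits participants by "age (18–24, 25–44, and 45–60 years"). No other section of the article states an eligible age range.

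**The concern.** A criterion with two bounds should set a floor and a ceiling. Here both signs are upper limits, so the 60-year limit has no effect and there is no floor. The printed rule would exclude nearly everyone the subgroup plan expects to analyse, and it would admit people under 18, for whom no subgroup band exists.

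This matters more than a slip in background text would, because the lower age bound decides whether people under 18 can enter. The article describes consent only as the participant's own signature, with no mention of a guardian's consent, which fits an adults-only intention. The criteria are used at five centres. Whether a participant's age is an eligibility deviation also has to be judged against the written bound.

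**Working it through.** No sample size, power or alpha figure is involved, so the check is a logical comparison of the two sections.

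**Inputs**
- Eligibility criteria, Table 1, criterion (1): age ≤18 and age ≤60.
- Additional analyses: bands 18–24, 25–44 and 45–60 years.

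**Step 1: reduce the criterion.** Anyone aged 18 or younger is also 60 or younger, so {age ≤18} ∩ {age ≤60} = {age ≤18}. The second condition adds nothing.

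**Step 2: find the range that the bands cover.** Counting ages in completed years:
- 18–24 has 24 − 18 + 1 = 7 ages.
- 25–44 has 44 − 25 + 1 = 20 ages.
- 45–60 has 60 − 45 + 1 = 16 ages.

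The total is 7 + 20 + 16 = 43, which equals 60 − 18 + 1. The bands therefore cover 18 to 60 without a gap.

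**Step 3: compare.**

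| Age group | Criterion (1) as printed | Subgroup plan |
|---|---|---|
| Under 18 | eligible | no band |
| 18 | eligible | band 18–24 |
| 19–24 | not eligible | band 18–24 |
| 25–44 | not eligible | band 25–44 |
| 45–60 | not eligible | band 45–60 |

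The overlap is 1 of the 43 ages, namely 18. It is not strictly empty, but the two sections cannot both stand.

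**Step 4: rule out a text-conversion fault.** The same table prints the opposite sign correctly in four other places: the transaminase limit (≥2.5 × ULN), the bilirubin limit (≥1.5 × ULN), the diastolic limit (≥100 mmHg) and the systolic limit, "sitting systolic blood pressure, ≥160 mmHg during the screening period". It also prints ≤ sensibly in exclusion criterion (9), at 90 mmHg. The two signs were kept distinct, so the fault most likely lies in the source text.

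**Step 5: infer the intended bound.** An upper limit of 60 has a purpose only if the first bound is a lower one, and the lowest band starts at 18. Both point to age ≥18 and ≤60.

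**The case against.** The strongest reply is that this is a misprint that corrects itself. The redundant upper limit and the subgroup bands leave no real doubt about the intended range, and no analysis depends on the sign. The article also introduces Table 1 as a summary. The approved protocol, version 1.1 according to Trial status, is not shown, and nothing indicates that sites screen from the journal table. A centre that applied the printed rule would turn away every adult over 18 and would soon notice.

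Most of this stands, and it limits the consequences. A reader might infer that the trial allows, or led to, enrolment of people under 18. The article does not support that: it does not show that any site document or the central randomisation system carries the wrong sign. A reader might also infer that the per-protocol set is left undefined on age. That does not follow either. The printed rule is well defined, only wrong; the intended rule is equally well defined; and exclusion from the per-protocol set depends on major deviations that affect evaluation of the primary outcomes. Nor is this a questionable design decision, since nothing suggests that anyone chose an upper limit of 18.

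The reply does not remove the error. An article may leave detail to the full protocol, but this is not missing detail. It is an eligibility threshold that is stated wrongly and contradicted by another section of the same document.

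**Conclusion.** The point holds as an internal contradiction, most likely caused by a sign error in the lower age bound. Read literally, criterion (1) and the subgroup plan agree only at age 18: two of the three bands would be empty and the first would be nearly so. This size describes the conflict between the two sections, not an expected effect on the trial.

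The conclusion rests on the printed text of the article and on the inference in Step 5. Any practical harm, whether enrolment of people under 18 or age deviations judged against the wrong limit, is conditional on the working documents repeating the error, and that cannot be settled from the article. Sample size, alpha and the primary analysis are unaffected.

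**What to change.** Correct inclusion criterion (1) in Table 1 to age ≥18 and ≤60 years, so that it agrees with the subgroup bands under Additional analyses. Then confirm that the approved protocol, the screening documents at all five centres and any eligibility check built into the central randomisation system carry the same bound. If any of them repeats the printed sign, correct it, and check the ages of participants already enrolled against the corrected range.

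The cost is one character in the table and a short document check. No analysis has to be changed.

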#### Recruitment and informed consent

Participants who are scheduled to undergo sedated upper gastrointestinal endoscopy in the outpatient gastrointestinal endoscopy operating room will be included in this study. They will be given an informed consent form, and they will be given the opportunity to review the consent and ask questions regarding the study. Interested participants will be screened using the inclusion and exclusion criteria. Eligible participants will sign an informed consent form. Study participation is voluntary, and the participants can withdraw from the study at any point of time. The recruitment and consent of the study participants by the members of the research team are in accordance with the Good Clinical Practice (GCP) guidelines. During the clinical trial, researchers will immediately report any serious adverse events occurring in the participants to the director-in-charge of the clinical trial of the research institution and will contact [name] or [name].

#### Allocation

Participants will be randomly assigned to one of the following three groups: experimental group 1 (remimazolam tosylate 0.15 mg/kg), experimental group 2 (remimazolam tosylate 0.2 mg/kg), or control group (propofol 1.5 mg/kg). A central randomization system will be used to randomize the participants. The system is stratified by each center, and the block length is six. Using the allocation sequence of the central randomization system, participants will be randomly assigned in a 1:1:1 ratio to experimental group 1, experimental group 2, or control group. Eligible participants will receive a unique random number upon enrollment. If multiple participants are scheduled on the same day, randomization will be performed based on the time of the participants’ arrival rather than the sequence of screening.

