#### Sample size

In this study, the noninferiority test will be performed between the experimental and control groups (i.e., experimental group 1 vs. control group; experimental group 2 vs. control group). Assume that the success rate of sedation in the propofol group is 100% and that in each remimazolam tosylate group is 95%. Considering the first type of error, *α* = 0.0125 (single-sided), 90% power, and 10% dropout rate, 600 participants are required for each group, with a total of 1800 for the three groups.

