##### Statistical analysis plan

All statistical analyses in this experiment will be programmed and calculated using the SAS analytics software version 9.4. In this study, the noninferiority one-sided test used for the main efficacy outcome is that a *P*-value of ≤0.0125 will be considered statistically significant. All other tests will be two-sided tests, with a *P*-value of ≤0.05 considered statistically significant, and the confidence interval will be set at 95%.

Measurement of basic data in different treatment groups will be statistically expressed as mean ± standard deviation or median (interquartile range [IQR]).

The *χ*^2^ test will be used for the success rate of sedation, incidence of injection pain, hypoxia, and adverse events. The analysis of variance will be used to induce time of sedation, full alertness, and discharge. The rank sum test will be used for calculating the satisfaction of endoscopists and participants.

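### Randomisation is stratified by centre, but the chi-square and rank sum tests named cannot use centre and the analysis of variance names no centre factor; the cost is modest, conservative and falls mainly on secondary outcomes

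*Protocol article*

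**What the plan says.** **Design.** In the Protocol article, Allocation, the central randomisation is described thus: "The system is stratified by each center, and the block length is six". In the same section, "participants will be randomly assigned in a 1:1:1 ratio to experimental group 1, experimental group 2, or control group". Eligibility criteria confirms the number of strata: "Participants will be recruited primarily from the abovementioned five centers".

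**Analysis.** The section headed Statistical analysis plan assigns a test to each outcome:

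- Binary outcomes, including the primary: the chi-square "test will be used for the success rate of sedation, incidence of injection pain, hypoxia, and adverse events".
- Time outcomes: "The analysis of variance will be used to induce time of sedation, full alertness, and discharge".
- Satisfaction: "The rank sum test will be used for calculating the satisfaction of endoscopists and participants".

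Centre is not mentioned in any of these. Additional analyses brings in other factors ("Subgroup analysis via an interaction by gender, age (18–24, 25–44, and 45–60 years), and BMI") but not centre. The section on nonadherence and missing data does not mention it either.

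**The concern.** Blocks within centre force the arms to be nearly equal in size at every centre, so differences between centres largely cancel out of the treatment comparison. An analysis that leaves centre out still counts those differences as noise. The estimated treatment effect hardly moves, but its reported standard error is larger than its true sampling error. Intervals come out too wide and P-values too large.

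A centre effect is plausible here. Top-ups are given as judged necessary, alertness and discharge readiness are scored by observers, endoscopists rate their own satisfaction, and only participants are described as blinded. At stake is some power in the secondary and safety comparisons, where a less sensitive test makes a real difference easier to miss.

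**Working it through.** **The plan's own figure.** Sample size gives success rates of 100% and 95%, α of "0.0125 (single-sided), 90% power, and 10% dropout rate", and 600 per group. The article states no non-inferiority margin, so 600 cannot be reproduced from its inputs alone. Solving backwards, a margin of about 8.3% fits: n = (2.2414 + 1.2816)² × (0.95 × 0.05) / (0.083 − 0.05)² = 12.41 × 0.0475 / 0.001089, about 542 evaluable. That is 603 after dividing by 0.9, or 597 after multiplying by 1.1. The margin is a separate matter. Here 8.3% serves only to carry a power calculation.

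**Time outcomes.** Let ρ be the share of outcome variance due to centre (assumed; the document gives none). With arms balanced within centre:

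- ratio of unadjusted to correct standard error = 1/√(1 − ρ)
- actual size of a nominal two-sided 5% test = 2 × [1 − Φ(1.960/√(1 − ρ))]
- power of the unadjusted test when the adjusted test has 90% = Φ(1.960 + 1.2816 − 1.960/√(1 − ρ))

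| ρ | SE overstated by | Actual α | Power, unadjusted |
|---|---|---|---|
| 0.01 | 0.5% | 4.9% | 89.8% |
| 0.05 | 2.6% | 4.4% | 89.1% |
| 0.10 | 5.4% | 3.9% | 88.0% |
| 0.20 | 11.8% | 2.8% | 85.3% |

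**Primary outcome, power.** With control at 100%, only the remimazolam arm contributes variance. Pooled variance is 0.95 × 0.05 = 0.0475. The within-centre part is 0.0475 − V, where V is the variance of the centre rates, so the ratio of stratified to pooled SE is √(1 − V/0.0475). A simulation (100,000 runs, five equal centres of 108 evaluable per arm, 8.3% margin, Wald tests) ran alongside.

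| Remimazolam success by centre (%) | V | Ratio, formula | Ratio, simulated | Power, pooled | Power, stratified |
|---|---|---|---|---|---|
| 95 in all five | 0 | 1.000 | 0.996 | 86.0% | 86.0% |
| 92, 93.5, 95, 96.5, 98 | 0.00045 | 0.995 | 0.992 | 86.3% | 86.3% |
| 90, 92.5, 95, 97.5, 100 | 0.00125 | 0.987 | 0.983 | 86.4% | 86.4% |
| 85, 92, 98, 100, 100 | 0.00336 | 0.964 | 0.961 | 86.9% | 87.8% |

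The 0.996 in the first row is not a gain. It arises because plug-in centre variances divide by n rather than n − 1: √[(107/108)/(539/540)] = 0.996. Power is near 86% rather than 90% because of binomial discreteness and the Wald approximation close to 100%.

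A further pattern gives a similar answer. Failure rates of 1, 2, 4, 6 and 12% have mean p(1 − p) = (0.0099 + 0.0196 + 0.0384 + 0.0564 + 0.1056)/5 = 0.0460, and √(0.0460/0.0475) = 0.984.

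**Primary outcome, type I error.** Here rates vary by centre in both arms, remimazolam is truly five points worse, and the margin is five points (illustrative). Nominal α is 0.0125.

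| Control success by centre (%) | Pooled Wald | Stratified Wald |
|---|---|---|
| 95 in all five | 0.0138 | 0.0145 |
| 92 to 98 | 0.0137 | 0.0144 |
| 85 to 100 | 0.0121 | 0.0145 |
| 75 to 100 | 0.0106 | 0.0139 |

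As centres diverge, the pooled test becomes more conservative, not less. Its slight excess when centres are alike belongs to the Wald method. The stratified Wald test sits a little above nominal throughout.

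**The case against.** **This is left to the SAP.** A journal article names test families, and model terms belong in a fuller document. That stands for the analysis of variance, which takes centre as a factor without changing its name. So a reader who infers that every planned test ignores centre goes further than the text. It does not stand for the other two: a chi-square test and a rank sum test have no centre term, and their stratified counterparts are different, separately named procedures.

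**The loss is assumed, not shown.** This stands. Any loss requires centre to be prognostic, and the document gives no between-centre data. The protocol also standardises much: top-up size and minimum interval, the sedation threshold, the definition of full alertness, the discharge score, and a narrow population.

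**It hardly touches the primary outcome.** This stands. Power is unchanged in three of the four scenarios and rises by 0.9 points in the fourth.

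**The remedy is not automatically better.** This stands for a stratified Wald test, which ran at 0.0139 to 0.0145 against 0.0125. It argues for a score-based interval, not for ignoring centre. The score-based version was not simulated here.

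**A stronger reading of the size.** A reader might equate ρ of 5% to 20% with throwing away that share of the sample. That is right for interval width but too strong for power, because the estimate itself keeps its precision. At ρ = 0.20, discarding a fifth of the sample would give Φ(3.2416 × √0.8 − 1.960) = Φ(0.939), or 82.6%. The unadjusted test keeps 85.3%.

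**Conclusion.** The mismatch between design and analysis is real for the chi-square and rank sum tests, and unresolved for the analysis of variance. If centre is prognostic, standard errors are overstated by about 0.5% to 12% for time outcomes (ρ from 1% to 20%), costing 0.2 to 4.7 points of power from 90%. For the primary outcome the figure is about 0% to 4% at the protocol's assumed success rates. These sizes rest on assumed centre differences and, in the simulations, on five equal centres.

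A reader might infer that the trial's validity is at risk, or that non-inferiority could be claimed falsely. The documents do not support this: leaving centre out makes the tests conservative. This is a modest point about efficiency, mainly for the secondary and safety outcomes, and worth acting on because the remedy is nearly free.

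**What to change.** State in the analysis plan, before any comparative data are seen, that centre is a stratum or factor in the comparative analyses:

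- **Success rate:** centre-stratified risk difference for each remimazolam group against propofol, with a score-based (Miettinen-Nurminen) confidence interval at the level matching one-sided 0.0125. Avoid a stratified Wald interval, given its simulated error rate and control rates expected near 100%.
- **Injection pain, hypoxia, adverse events:** Cochran-Mantel-Haenszel test stratified by centre.
- **Induction, alertness and discharge times:** centre as a factor in the analysis of variance.
- **Satisfaction:** van Elteren (stratified rank sum) test.

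The cost is a few sentences and the matching code. Centre is already known from randomisation, and neither data collection nor sample size changes. Fixing it in advance also removes any later choice between adjusted and unadjusted results.

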#### Allocation masking

This study follows a single-blinded method. All participants are blinded to the assignment of the trial (the injection site will be shielded) and will be randomly assigned to any of the three groups.

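### One fixed, stated block length of six per centre, with only participants blinded, makes up to one allocation in five predictable to enrolling staff who know the length and count past allocations

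*Protocol article*

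**What the plan says.** The Allocation section of the protocol article sets up the scheme in three statements. The mechanism is central: "A central randomization system will be used to randomize the participants". The block structure is a single value within each centre: "The system is stratified by each center, and the block length is six". The ratio is equal: "participants will be randomly assigned in a 1:1:1 ratio to experimental group 1, experimental group 2, or control group". For several participants on one day, "randomization will be performed based on the time of the participants’ arrival rather than the sequence of screening".

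Under Allocation masking, the article states "This study follows a single-blinded method" and "All participants are blinded to the assignment of the trial", achieved by shielding the injection site. It describes no masking of staff. Under Procedure of the trial, both the initial dose and the top-up drug depend on the assigned group, so whoever doses a participant knows that participant's arm.

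Under Recruitment and informed consent, members of the research team recruit and obtain consent. Exclusion criterion 13 in Table 1 lets the investigator exclude someone on "judgment as an unsuitable participant".

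**The concern.** Central randomisation hides the list, but it does not hide allocations already made and seen. With one known block length, a person who has seen all earlier assignments at a centre can work out what is left in the current block. Near the end of a block, the next assignment is sometimes certain.

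Someone with that knowledge who also controls entry could decline or defer a participant, and the judgment-based exclusion would be an available reason. If that happened, the arms could differ in how easily their participants are sedated, and the difference in success rates would be biased. The article plans neither a data-monitoring committee nor auditing of trial conduct, so neither would be there to detect it.

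**Working it through.** The protocol gives no predictability figure, so there is none to reproduce.

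**Inputs.** Block length 6 within centre and ratio 1:1:1 (Allocation), hence 2:2:2 per block; total 1800 and assumed remimazolam success of 95% (Sample size); five centres (Study setting). Assumption not in the documents: the observer knows the block length and every earlier arm at the centre, including the remimazolam dose.

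**Enumeration.** There are 6!/(2!·2!·2!) = 90 equally likely sequences. An allocation is certain when only one arm has slots left. The best guess is the arm with most slots left, right with probability (largest remaining count)/(slots remaining).

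| Position | Remaining counts (probability) | P(certain) | P(best guess right) |
|---|---|---|---|
| 1 | 2,2,2 (1) | 0 | 2/6 = 0.333 |
| 2 | 1,2,2 (1) | 0 | 2/5 = 0.400 |
| 3 | 0,2,2 (1/5); 1,1,2 (4/5) | 0 | 2/4 = 0.500 |
| 4 | 0,1,2 (3/5); 1,1,1 (2/5) | 0 | 0.6×2/3 + 0.4×1/3 = 0.533 |
| 5 | 0,0,2 (1/5); 0,1,1 (4/5) | 0.20 | 0.2×1 + 0.8×1/2 = 0.600 |
| 6 | 0,0,1 (1) | 1.00 | 1.000 |

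- Certain: (0.20 + 1.00)/6 = 1.2/6 = 20.0%. Cross-check at position 5: 18 of the 90 sequences end in the same arm twice, and 18/90 = 0.20.
- Best guess: (0.333 + 0.400 + 0.500 + 0.533 + 0.600 + 1.000)/6 = 3.367/6 = 56.1%, against 1/3 by chance.
- Scaled up: 0.20 × 1800 = 360, or 72 per centre if the five centres recruit equally (an assumption).

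**Drug only.** An observer who sees the drug but not the remimazolam dose counts a 4:2 block. The next drug, though not the dose, is then certain for 1.733 of 6 allocations, or 28.9%. Counting therefore still works without knowledge of the dose.

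**Randomly mixed blocks.** Simulation with 360 participants per centre and an observer who knows the set of sizes but not their order:

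| Block sizes | Certain | Best guess right |
|---|---|---|
| 6 only | 20% | 56% |
| 3, 6 | 9% | 58% |
| 6, 9 | 5% | 54% |
| 3, 6, 9 | 4% | 55% |
| 6, 9, 12 | 2.5–2.6% | 53% |

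**Scale of a possible effect (illustration).** With the planned 5% failure rate on remimazolam, suppose selection removed every failure in the certain slots and nowhere else. The success rate in a remimazolam arm would rise by 0.20 × 5 = 1.0 percentage point; halving those failures gives 0.5 point. Acting on mere guesses could add to this, and selection of harder cases would reverse the sign.

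**The case against.** The strongest reply is that the key premise is not in the documents. Nothing says that the people who screen and enrol see all earlier allocations at their centre, or that they are the people who dose. The 20% needs an unbroken centre-wide tally and knowledge of the block length. The length stands in this article, but the documents do not show when sites learned it. This objection stands: 360 is a ceiling under those conditions. A reader might infer that 360 allocations are in fact known in advance or that concealment has been lost, and the text does not support either.

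Second, arrival-time ordering removes the option of reshuffling a day's list, so using a prediction would mean turning away or postponing someone who has come for a scheduled endoscopy. The population is also narrow (upper age 60, ASA I–II, BMI between 18 and 28, no heart or lung disease), which leaves less room to pick easy cases. Both points reduce the opportunity, but neither removes it.

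Third, a reader might infer that any bias would favour noninferiority. That assumes staff favour remimazolam, and no section says so.

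Fourth, the remedy cuts certainty far more than guessing: 56% to about 53%. This is correct, and selective enrolment can act on a good guess. The gain is that the slots known for sure almost disappear.

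Finally, a fixed block of six is consistent with the 1:1:1 ratio, so the protocol contains no error or contradiction here. The point is about a design choice.

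**Conclusion.** The point holds as an avoidable weakness in the allocation scheme. A single stated block length of six, used within centre while staff are unblinded, makes up to 20% of allocations certain and gives a best-guess accuracy of 56% against 33% by chance. Both figures are exact for 2:2:2 blocks and are averages over complete blocks. They rest on the enrolling person knowing the block length and every earlier arm at the centre, which the documents neither state nor rule out. What is established is an opportunity for selection bias, of unknown direction and unquantified effect. It is worth correcting because correction is cheap; it does not by itself put the trial's result in doubt.

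**What to change.** Have the central system draw each block size at random from several multiples of three, for example 6, 9 and 12, within centre. Keep the sizes out of site-facing documents; the protocol text need only say that block sizes vary and are withheld from sites. If enrolment has started, apply this to the allocations still to be made.

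The cost is one system setting and one sentence. Within a centre, the gap between two arms at any moment could reach 4 (half-used block of 12) where it can now reach 2, which is negligible at 600 per arm. The change should be described as removing most certain predictions, from 20% to about 2.6%. It does little against guessing, which remains right about 53% of the time.
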